Despite literature suggesting improvements in appropriate antibiotic prescribing (right drug, dose, and duration when antibiotics are truly needed) are achievable and yield better patient outcomes, effective and sustained implementation remains elusive. Shifting threats to adherence, including those internal to a system or environment as well as external factors (e.g. case mix changes) often undermine gains from previous implementations. Therefore, we aim to utilize the following strategies in combination to enact large-scale, sustainable implementation: 1) audit and feedback, 2) clinical decision support tools in the EMR to guide clinicians at the point of care to recommended narrow-spectrum antibiotics for the recommended duration, 3) clinician champions and local leaders to influence peers and sustain focus on stewardship goals, 4) educational outreach with updated and regularly renewed system guidelines and resources for each respiratory condition and peer stewardship partners to provide personalized training and problem-solving with clinicians to address knowledge gaps, concerns, and misconceptions, and 5) patient education and engagement via brochures, shared-decision making aids, or other approaches to help clarify caregiver expectations about antibiotics when appropriate, their role, and symptomatic management. Each of these strategies has shown promise in controlled or smaller-scale studies. The challenge remains how to integrate and scale all of these tactics in a unified ambulatory stewardship intervention across the varied care delivery environments of a geographically dispersed large health system that realizes and sustains improvements in antibiotic prescribing.

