### Study procedures

This evaluation will use observational and quasi-experimental designs to examine effectiveness and implementation outcomes as outlined below. The implementation will proceed in two waves with approximately half of the sites in each wave. To maximize efficiency and likelihood of adoption, sites will be assigned to waves based on region rather than by randomization (see Fig. 2). The first wave includes all sites in the Canyons region with Peaks and Desert regions in the second wave. Each wave will provide a pre-post design using archival baseline data. In addition, the Peaks and Desert regions serve as a comparison group for the Canyons implementation to compensate for possible secular trends. We plan to examine adherence rates overall (aim 1), across sites (aim 2), and as a function of response to Boost (aim 3).

In addition, we plan to examine the use of implementation strategies overall (aim 1), across sites (aim 2), and in response to Boost (aim 3). This examination is based on several key indicators including: the number and frequency of trainings, attendance at trainings, and the frequency with which providers and sites access tools such as EMR utilities (e.g., preference lists, order sets, smart sets), c-SMART dashboards, and audit & feedback reports. We expect that the use of these strategies will vary by site and correlate with changes in adherence.

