### Data collection and analysis

Data collection will rely primarily on observational EMR data extracted from approximately 250 Intermountain Health sites, encompassing all pediatric encounters for indicated acute respiratory tract infections where antibiotics were prescribed during the study period. Baseline data from the 12 months prior to implementation will establish pre-intervention prescribing patterns, and ongoing EMR data abstraction will capture antibiotic selection, duration, and encounter-level covariates. Statistical analyses will follow a quasi-experimental pre–post design with staggered regional implementation, employing age, diagnosis, provider specialty, and care setting as covariates in linear probability models and using generalized estimating equations to account for clustering at the provider level. Clinic rurality and patient-level rurality, race, ethnicity, and preferred language may be controlled for if not deemed to be too collinear and not deemed as having too much missingness. The first three months of intervention will be considered an implementation rollout period and analyzed accordingly. Power calculations indicate > 99% power for a test at alpha = 0.05 to detect a ≥ 5% improvement in adherence across an estimated 356,000 encounters expected during the study period. If there is an overall effect, testing for each region separately will be conducted with Bonferroni-Holm adjustment for the three tests; if not significant, the region-specific tests will still be conducted but interpreted as exploratory.

Additional analyses will include interrupted time-series analysis and segmented regression to assess temporal trends, as in recent work [44]. Subgroup analyses will examine demographic covariates (e.g., ethnicity, language, insurance) and other characteristics (e.g., site rurality, setting type). Analyses will generally be conducted using robust variance estimators, unless explicit modeling of correlations is indicated (e.g., interrupted time-series analysis).

The Aim 3 analyses of Boost will proceed in an analogous manner, focusing on covariate-adjusted comparisons of adherence for encounters during the active implementation phase where Boost is in use to encounters during the active implementation phase where Boost is not in use.

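### Clustering only by provider leaves out correlated change within sites, so standard errors are probably too small; cluster by site instead

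*Protocol article*

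**What the plan says.** All references are to the protocol article.

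- **Model.** Data collection and analysis specifies linear probability models "using generalized estimating equations to account for clustering at the provider level". The same section adds: "Analyses will generally be conducted using robust variance estimators, unless explicit modeling of correlations is indicated". It names neither site nor region as a cluster.
- **Assignment.** Under Study procedures, "sites will be assigned to waves based on region rather than by randomization". Canyons forms wave 1; Peaks and Desert form wave 2 and also serve as the comparison group for Canyons.
- **Variation by site.** Study procedures expects uptake of the strategies to differ between sites and to go along with changes in adherence. The Background lists "clinician champions and local leaders to influence peers and sustain focus on stewardship goals" among the strategies.
- **Boost.** Methods and design and the Aim 3 hypothesis give Boost to selected sites. Data collection and analysis says that its analysis will follow the main one.
- **Power.** "Power calculations indicate > 99% power for a test at alpha = 0.05 to detect a ≥ 5% improvement in adherence". The figure is given for all of the roughly 356,000 encounters that the study anticipates. No baseline rate, intracluster correlation or design effect is given.

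**The concern.** A sandwich variance allows for correlation inside the declared cluster and for none between clusters. With the provider as cluster, two clinicians at the same site count as independent, although they may share a champion, local training, case mix and Boost status. The protocol's own expectation that uptake and change differ by site describes the component that is left out.

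If that component is not zero, standard errors are too small and tests reject too often. This affects the overall test, which decides whether the Holm-adjusted region tests are confirmatory or exploratory, and then the region tests themselves.

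Two kinds of comparison are more exposed:

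- **Rurality and setting type** are attributes of sites, so part of each such contrast lies between sites, where stable site differences do not cancel.
- **Boost** compares encounters with and without Boost during active implementation. It is partly between sites and rests on fewer treated sites.

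**Working it through.** **Inputs from the protocol:** about 250 sites, about half in each wave; 356,000 encounters; alpha 0.05; a 5% improvement, read as 5 percentage points because the model is a linear probability model.

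**Assumptions, not in the protocol:** equal pre and post halves of 178,000 encounters; 8 providers per site (2,000 in all); provider-by-period SD of 5 points; site-by-period SD τ of 0 to 5 points; two-sided tests.

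**1. The plan's own figure.** With baseline 50% and independent encounters, SE = 100 × √(2 × 0.25/178,000) = 0.168 point. Five points is about 30 SEs. Power computes to 1.000 for every baseline from 50% to 80%, one- or two-sided. At a 50% baseline, 99% power needs 3,661 encounters per period, so the claim survives a design effect of 178,000/3,661 ≈ 48.6. It reproduces.

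**2. Pooled pre-post contrast, true against provider-clustered SE** (points):

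- True variance = 2τ²/250 + 2 × 5²/2,000 + 0.168²
- Provider-clustered variance = 2τ²/2,000 + 2 × 5²/2,000 + 0.168²
- Null rejection rate = 2 × [1 − Φ(1.96 × clustered SE / true SE)]

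For τ = 5 the true variance is 0.200 + 0.025 + 0.028 = 0.253, and the clustered variance is 0.025 + 0.025 + 0.028 = 0.078.

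| τ (points) | True SE | Provider-clustered SE | Type I error, formula | Type I error, simulated |
|---|---|---|---|---|
| 0 | 0.23 | 0.23 | 5% | not run |
| 2 | 0.29 | 0.24 | 11% | 12% |
| 3 | 0.35 | 0.25 | 17% | 19% |
| 5 | 0.50 | 0.28 | 28% | 30% |

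The simulation used 1,500 replicates per scenario. With 4 to 16 providers per site its range is 9% to 37%. Site clustering restores about 5%.

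**3. Canyons versus Peaks and Desert.** A separate simulation of the difference-in-differences used 125 against 125 sites, 8 providers per site, 45 encounters per provider and period, baseline 60% and no regional shock. Provider-clustered rejection under the null is 4.9%, 9.5%, 23.9% and 33.9% at τ = 0, 2, 5 and 8 points. At τ = 5 the mean provider-clustered SE is 0.64 point against a true 1.05, about 40% too small. Site-clustered rejection is 4.4% to 5.3%.

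**4. Power with site clustering.** Pooled pre-post power for 5 points is at least 0.9998 for τ up to 10 points. For the controlled contrast with half of the encounters usable, it is 1.000, 0.999, 0.914 and 0.772 at τ = 2, 5, 8 and 10.

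**5. What site clustering does not repair.** Let ω be an assumed region-by-period SD. With one region against two it adds 2ω²(1 + 1/2) = 3ω² to the variance of the controlled contrast. At ω = 1 point, site-clustered tests still reject 18% to 53% of true nulls over the τ values in step 3. At τ = 5, power allowing for the regional term (normal reference) is 0.70 at ω = 1 and 0.28 at ω = 2.

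**The case against.** **The size is assumed.** The protocol gives no site-by-period SD, provider-by-period SD or number of providers per site, and with no site-by-period variation provider clustering is adequate. This stands, so a flat statement that type I error is inflated would go too far. The protocol's own expectation of variation by site makes the zero case unlikely, but does not size it.

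**The general phase is not very local.** The contributions summary describes it as having little site-level focus, the dashboard system is standardized, and start dates follow the regional wave. This weakens the case for a large site component in the primary analysis. It does not help Boost, which is delivered to sites.

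**The main conclusion is hardly at risk.** In the table above, a true 5-point effect lies about 10 or more SEs from zero even with the correct SE (5/0.50). This stands: only small effects in the pooled test could change significance.

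**The limitations are disclosed.** Challenges and limitations concedes that the lack of randomization weakens causal inference. It does not address the clustering level, and the interrupted time series is an additional analysis that leaves the primary model's SE unchanged.

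A reader might also infer that the power above 99% is wrong. The document does not support that: it claims the figure for an improvement over all encounters, where it reproduces and survives site clustering. It claims nothing for the controlled comparison.

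**Conclusion.** The concern holds for the level of clustering. The text fixes the provider level, while the protocol's own account of delivery and expected variation points to correlated change within sites. For assumed site-by-period SDs of 2 to 5 points, with 8 providers per site, type I error is about 10% to 30% against a nominal 5%; at zero it is about 5%. The practical weight falls on Boost, region-specific, site-level subgroup and small-effect comparisons rather than on a 5-point pooled effect.

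The power sentence is correct for the contrast it describes. It should not be carried over to Canyons versus Peaks and Desert.

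It is also tempting to treat site clustering as the answer to assignment by region. It is not: with one region against two, regional drift stays outside the standard error, and three regions are too few for a region-level sandwich variance.

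**What to change.** In Data collection and analysis, change the clustering level from provider to site, with providers nested in about 250 site clusters. Assign providers who work at several sites to their main site, or use two-way clustering. Apply this to the primary, region-specific, subgroup and Boost analyses.

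The power sentence can stay. Report the Canyons versus Peaks and Desert comparison with the caveat that its intervals do not include region-by-period drift.

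The cost is one word in the model description, a rule for providers at several sites, and wider intervals. No new data are needed, and 250 clusters are ample for a robust variance; contrasts that rest on few Boost sites will have correspondingly wide intervals.

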### Primary innovation

Two complementary best practices will be tested: the primary outcome is adherence to recommended antibiotic *selection*.

Secondarily, we will examine adherence to recommended *duration*, as well as the combination of *selection and duration* (i.e., RADAR; see Fig. 5 in Supplementary Information). Prescriptions will be considered guideline-concordant if the antibiotic matches the recommendations in Table 1. Based on preparatory examination of data and charts, we will allow a 1-day window below or above the recommended duration (e.g., 4–6 days for 5 days).

**Table 1 Tab1:** Recommendations for selection and duration based on ARTI condition

Condition	Age	Antibiotic	Duration
Acute Otitis Media	6 months—2 years old	Amoxicillin	10 days
	2–5 years old		5 days
	> 5 years old		5 days
Sinusitis	< 18 years old	Amoxicillin	5 days
Group A strep Pharyngitis	> 6 months old	Amoxicillin or Penicillin	10 days
Community Acquired Pneumonia	> 3 months	Amoxicillin	5 days

### Primary effectiveness and implementation outcomes

SCORE-Peds assigns value to both clinical effectiveness and implementation outcomes. Effectiveness outcomes will focus on improvements in guideline-concordant antibiotic prescribing for pediatric ARTIs.

The primary effectiveness outcome, which is the overall primary outcome with analyses as previously described, is the *antibiotic selection*– specifically the proportion of encounters in which a *narrow-spectrum antibiotic* is prescribed out of all ARTI encounters where any antibiotic was prescribed.

The primary implementation outcome will be two measures of *adoption* at the prescriber and site level. The measures of adoption are derivatives of the primary effectiveness outcome. Specifically, adoption is defined as the proportion of *prescribers* who have 80% adherence to antibiotic selection in their encounters, and the proportion of *sites* with 80% of prescribers considered adherent to antibiotic selection.

### Secondary effectiveness outcomes

An important secondary outcome is the proportion of encounters with an appropriate *duration* of antibiotic therapy out of all encounters where any antibiotic was prescribed. Appropriate duration is defined based on Table 1. The other secondary effectiveness outcome is the proportion of encounters with *both guideline-concordant selection and duration*. To facilitate consistent messaging with all stakeholders across our large health system, to describe this *R*ecommended *A*ntibiotic and *D*uration *A*dherence *R*ate we developed the acronym RADAR for this composite adherence measure (see Fig. 5 in Supplementary Information). This secondary effectiveness outcome is a more rigorous composite adherence measure that focuses on whether each antibiotic prescription for a target condition met both the recommended antibiotic selection and the recommended duration.

### Other outcomes

Treatment failure will be examined as a balancing measure and defined as a return visit between 2 and 14 days for the same ARTI diagnosis where a new antibiotic prescription was given.

In terms of implementation, the study will evaluate the proportion of sites using clinical decision support tools (e.g., preference lists for antibiotic selection and duration), the percentage of clinicians engaging with audit-and-feedback dashboards, and indicators of implementation engagement such as attendance at trainings, and participation in site facilitation.

### Data management

Study data will be collected from IH’s integrated electronic medical record (EMR) system and the corresponding IH enterprise data warehouse. These data will be used to report results to internal and external audiences supporting the ongoing QI. IH implemented a common EMR in September of 2025. Where available, baseline data from 2023–2025 will be collected to examine secular trends and inform the impact of the QI initiatives in 2026–2029. Data will include patient demographics, encounter data, medication and prescription information, area deprivation index (ADI) and other indicators of socio-economic status (e.g. RUCA codes), insurance data, care site characteristics (e.g., number of caregivers/prescribers at site, location of care site).

Evaluation of the project will include (1) the use of internal dashboards and reports to inform the QI process (i.e., formative evaluation), and (2) the use of robust statistical methods to evaluate the goals of the project (i.e., summative evaluation). For internal evaluation (1), Intermountain analysts will build dashboards and reports typical of quality improvement projects. For robust statistical analysis (2), the University of Utah Data Coordinating Center (DCC) will provide expert statistician support employing the analytic techniques described previously.

All data will be secured using established Intermountain policies for internal use and for the protection of research data. This includes oversight by the IRB at IH. Datasets used for advanced statistical analyses and summative evaluation will be protected as research data. This includes limiting access to evaluation personnel with appropriate research training, securing data when stored, and transmitting via encrypted channels.

## Discussion

Improving ambulatory antibiotic use in pediatrics remains a challenge and imperative for health systems. The SCORE-Peds project will provide significant insights for implementing antibiotic stewardship best practices at scale in a large geographically dispersed health system. To our knowledge, this is the first attempt to deploy a unified stewardship intervention across such a broad ambulatory network (250 sites) in real-world practice. This contrasts with prior stewardship studies which have been limited in scope – for example, focusing on a subset of clinics or a single region, or conducted as tightly controlled trials. By undertaking this system-wide approach, our study will yield practical learnings regarding logistics, effectiveness, differential impacts, and sustainability of scaling evidence-based antibiotic stewardship practices into routine care.

One anticipated benefit of operating at scale will be the ability to study contextual variation. With hundreds of sites involved and differences between each of our three distinct regions, we will be able to characterize how different settings respond to the same intervention with real-world experience. For instance, factors such as clinic size, rural vs urban patient population, care delivery setting, or baseline prescribing cultures may impact outcomes. We will be able to examine, for example, whether rural pediatric or family medicine clinics encounter different barriers to achieving high prescribing rates for narrow spectrum shorter duration prescriptions compared to large urban UC or ED clinics and how those barriers might be overcome. Such knowledge is highly valuable – large health systems often struggle with how to tailor improvement strategies to diverse practice environments. Our findings could inform guidance on what core components of an intervention need adaptation when spreading to new contexts versus what is more generalizable and can be standardized.

One notable innovation of this study is the use of the RADAR metric to track prescribing quality as a secondary effectiveness outcome. By linking the numerator to guideline-concordant prescriptions (recommended narrow spectrum antibiotic for the recommended duration) and the denominator to all encounters for the conditions of interest in which an antibiotic was prescribed, RADAR emphasizes adherence to clinical best practices at each opportunity. Traditional volume-based measures that simply count antibiotic prescriptions cannot distinguish recommended from inappropriate antibiotic use and may be less actionable in settings where overall prescribing rates are either already low or less amenable to interventions to decrease high prescribing rates. In contrast, RADAR directly highlights the appropriateness of therapy, aligning with stewardship goals of “right antibiotic, right duration” rather than simply decreasing prescription volume. There are however, unique considerations to RADAR. Clinical features such as case mix, severity, and prior history with antibiotics may not be easily captured. Like other metrics, RADAR may fail to fully capture important contextual nuances that can justify practices that deviate from guideline recommendations. It should be interpreted alongside clinical context, and qualitative feedback or case review may be needed to understand outliers. Nonetheless, the potential for RADAR to be used broadly in outpatient settings is significant, especially in health systems where prescription volume alone provides limited insight and our study will provide an opportunity to better understand its utility in a variety of ambulatory settings.

This study also includes a “Boost” phase wherein resources and efforts are directed to sites with lower adoption rates following an initial implementation. This design reflects an implementation intensification approach, augmenting low-touch tactics with high-touch support at sites in need of specialized support. Such strategies are increasingly recommended for scaling evidence-based practices in large health systems [45, 46]. Examining which contexts benefit the most from Boost will inform how to efficiently adapt and scale stewardship efforts across a large integrated health system. Importantly, if low-adoption sites do not improve with "Boost” efforts, this too will be an important learning and suggest that more intense application of certain stewardship strategies may not be the solution for sites and settings whose narrow-spectrum antibiotic prescribing rates for the recommended duration remain low. While our primary outcomes are focused on prescribing behavior, the ultimate goal is to improve patient health and experience, consistent with the Patient Centered Outcomes Research Institute’s (PCORI) mission. By reducing unnecessarily broad-spectrum antibiotic use and shortening antibiotic prescriptions when appropriate, we aim to decrease side effects and complications for children. We will indirectly assess patient-centered outcomes such as symptom resolution and satisfaction via treatment failure and leverage patient satisfaction survey data already a part of our health system standard patient experience to identify potential signals regarding antibiotic selection, duration, and RADAR.

